## Abstract

**Background:**

Weight gain can be a consequence of stroke, or cerebrovascular accident (CVA), because of impaired mobility, behavioral and emotional disorders, and sensory losses. Weight gain increases the patient’s risk of recurrent stroke and chronic diseases, such as diabetes, metabolic syndrome, and pulmonary and heart disease. Approaches to weight loss in this population are lacking, although necessary because of the unique physiological and cognitive needs of persons after a stroke. Evidence shows that intensive behavioral therapy interventions that address both physical activity and diet offer the greatest potential for weight loss. The Group Lifestyle Balance (GLB) intervention is a 12-month, evidence-based weight loss program that has been used extensively with the general population; this program was modified to meet the needs of people who have had a stroke (GLB-CVA).

**Objective:**

This randomized controlled trial (RCT) aims to examine the efficacy of the GLB-CVA on weight and secondary outcomes, compared with that of a waitlist control group.

**Methods:**

This RCT will enroll and randomize 64 patients over an 18-month period.

**Results:**

Currently, 51 people are waitlisted, with 23 out of 51 screened and 16 out of 23 eligible.

**Conclusions:**

It is anticipated that the findings from this RCT will contribute to the evidence base regarding weight loss strategies for people living with stroke.

**Clinical Trial:**

ClinicalTrials.gov NCT03873467; https://clinicaltrials.gov/ct2/show/NCT03873467

## Introduction

### Background

Stroke, or cerebrovascular accident (CVA), is a serious public health issue because of its high incidence, high cost of care, and increased risk of morbidity and mortality [1]. Projections show that by 2030, an additional 3.4 million people aged >18 years will have had a stroke, which is a 20.5% increase in prevalence from 2012 [2]. Estimates indicate that about one-third of stroke survivors have excessive weight, causing them to be overweight or obese (body mass index or BMI ≥25 kg/m^2^) [3]. Weight gain significantly restricts functioning and independence and greatly increases the risk of chronic diseases, such as diabetes, metabolic syndrome, pulmonary disease, heart disease, and recurrent stroke [4,5].

There is a high prevalence of weight gain and obesity after stroke, as people’s physical activity and healthy eating behaviors are negatively impacted [3]. This may be because of a combination of personal (eg, low motivation and lack of social support) and environmental factors (eg, lack of transportation, high cost of specialized programming, and lack of education from health care providers) [6]. Yet, increased physical activity and healthy dietary habits are recognized approaches to reduce the risk of comorbidities, such as obesity, hypertension, diabetes, recurrent stroke, and heart disease [7]. However, there is a lack of evidence-based approaches to weight loss for people after stroke [8]. Most currently available evidence-based weight loss programs were developed and tested with samples from the general population, with *disability* often used as an exclusion criterion [9,10]. Thus, the appropriateness of these programs to meet the unique needs of people who have had a stroke is unknown.

The Group Lifestyle Balance (GLB) program is a 12-month self-management intervention that has been shown to result in weight loss and reduce the risk for type 2 diabetes through improved physical activity and healthy eating behaviors [11-15]. Although the GLB has been used extensively with the general population [16,17], no study has been conducted specifically for people who have had a stroke. This protocol describes a randomized controlled trial (RCT) that will assess the efficacy of the GLB program that has been modified with input of stroke survivors (GLB-CVA). The GLB-CVA program will be compared with a waitlist control group. This protocol followed the standard protocol items: recommendations for interventional trials checklist to report relevant clinical trial details, as recommended by the Enhancing the Quality and Transparency of Health Research Network.

### Objectives

#### Aim 1

Aim 1 of this study is to examine adherence to GLB-CVA intervention participation.

*Hypothesis:* Intervention participants will attend at least 70% (15/22) of the weekly and monthly group-based sessions [18].

#### Aim 2

Aim 2 of this study is to conduct an RCT to examine the efficacy of the GLB-CVA on primary and secondary outcomes in the intervention group, compared with the waitlist control group at 3 and 6 months from baseline.

*Hypothesis 2.1:* The intervention group will demonstrate statistically significant improvements in our primary (weight) and secondary outcomes (activity assessed with accelerometers, waist and arm circumference, blood pressure, hemoglobin A_1c_, fasting glucose and lipid panel, 8-year diabetes risk, functional measures, self-report measures of physical activity and healthy eating, executive function, perceived social support, self-rated abilities for health behavior practices, pain interference, sleep disturbance, habits, and quality of life) when compared with the waitlist control group at 3 and 6 months.*Hypothesis 2.2:* Combined intervention data from both groups will demonstrate significant improvements in primary and secondary outcomes after 3, 6, and 12 months.

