### Intervention

The GLB intervention promotes self-management of a healthy lifestyle based on the tenets of Social Cognitive Theory [20] and the Health Belief Model [21]. The GLB program facilitates individual engagement in health behavior change and is completed in a group setting [11-15]. Data from previous GLB trials have shown 5% to 7% weight loss in a variety of settings, including community centers, churches, worksites, and health care systems [13,16,22-28]. The goal for participants is to reach 150 min of physical activity following the American Heart Association’s (AHA) recommendations and follow dietary guidelines by the United States Department of Agriculture. The GLB program comprises 22 sessions over 12 months, including 12 weekly core program sessions, 4 transition phase sessions, and 6 support sessions (see Multimedia Appendix 1). GLB program materials are made available to the public under the Creative Commons licensing agreement through the Diabetes and Prevention Support Center at the University of Pittsburgh that developed the GLB program.

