### Statistical Methods

To examine adherence to the GLB-CVA intervention (Aim 1), univariate analysis will be used to summarize session attendance to determine if it reaches the hypothesized rate of at least 70% (15/22). An RCT will be completed to examine the efficacy of the GLB-CVA on primary and secondary outcomes in the intervention group compared with the waitlist control group at 3, 6, and 12 months from baseline. General mixed modeling analysis will be conducted for the primary and secondary outcomes to assess initial and sustained impacts of the adapted GLB-CVA intervention. More specifically, individual growth models will be evaluated for linear and nonlinear change from baseline to 3, 6, and 12 months (level 1, time effects), overall group difference (level 2, group effect), and group difference in change (cross-level, time-by-group interaction effect; Hypothesis 2.1). Models will be adjusted for demographic variables (eg, age, gender, ethnicity, and disability severity using the Modified Rankin Scale), particularly if they are imbalanced after randomization, thereby providing more accurate estimates of the intervention impacts.

Separate growth models for change from baseline to 12 months will be fitted within both groups combined (time effects only; Hypothesis 2.2). Data will include missing observations resulting from either attrition or nonresponse. Intent-to-treat analysis will use restricted maximum likelihood estimation, which can produce unbiased estimates with incomplete data. In addition, sensitivity analysis will utilize iterative Monte Carlo Markov Chain multiple imputation for missing data. All selected variables will be used in the imputation process, allowing for greater recovery of the missing data. All analyses will be performed using SAS 9.4.

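### The Aim 1 adherence threshold is internally inconsistent: 15 of 22 sessions is 68.2%, which falls short of the 70% minimum it is said to represent

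*Protocol article*

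**What the plan says.** Aim 1 concerns adherence to the intervention. Under Objectives, the protocol article states the hypothesis that "Intervention participants will attend at least 70% (15/22) of the weekly and monthly group-based sessions".

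The Statistical Methods section carries the same figure into the analysis: "univariate analysis will be used to summarize session attendance to determine if it reaches the hypothesized rate of at least 70% (15/22".

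The denominator is confirmed under Intervention: "The GLB program comprises 22 sessions over 12 months, including 12 weekly core program sessions, 4 transition phase sessions, and 6 support sessions".

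The article does not describe 15 as a rounded or approximate figure, and it does not say whether the percentage or the count takes precedence.

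**The concern.** The percentage and the count in brackets are presented as one threshold, but they are two. The wording sets a minimum, and the count offered as its equivalent lies below that minimum. Because the pairing appears both in the hypothesis and in the analysis that addresses it, neither place can be used to correct the other.

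This is the only criterion the article gives for Aim 1. Attendance is to be compared with it, so a result between the two values would support the hypothesis on the count and not on the percentage. What is at stake is whether one descriptive hypothesis has a single, fixed pass mark.

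**Working it through.** **Inputs, all from the protocol article**

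- Threshold as a percentage: at least 70% (Objectives, Aim 1; repeated in Statistical Methods).
- Threshold as a count: 15 of 22 (same two places).
- Number of sessions: 12 core + 4 transition + 6 support = 22 (Intervention).

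**Step 1. Try to reproduce the stated equivalence.**
15 / 22 = 0.6818, or 68.2%. This is below 70% by 70.0 − 68.2 = 1.8 percentage points. The stated figure does not reproduce.

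**Step 2. Find the count that the percentage implies.**
0.70 × 22 = 15.4 sessions. A person attends a whole number of sessions, so a minimum of 70% requires rounding up, to 16. Rounding to the nearest integer, or down, gives 15. That is the likely origin of the printed figure, but it is not compatible with a minimum.

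| Sessions attended | Share of 22 | Meets 15/22 | Meets 70% |
|---|---|---|---|
| 14 | 63.6% | no | no |
| 15 | 68.2% | yes | no |
| 16 | 72.7% | yes | yes |

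**Step 3. Check whether another denominator rescues the figure.**
15/21 = 71.4% and 15/20 = 75.0% would both satisfy the percentage. However, the article fixes 22 sessions, and the bracketed fraction itself uses 22.

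**Step 4. Find where the two readings give different answers.**

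- If attendance is judged as a group mean: for means from 15.0 to just under 15.4 sessions, that is, 68.2% to just under 70%.
- If adherence is counted per participant: for anyone who attends exactly 15 sessions.

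Outside these cases the readings agree.

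**Step 5. Check the alternative wording.**
0.68 × 22 = 14.96, so a minimum of 68% is first met at 15 sessions. A threshold of at least 68% (15/22) would therefore be self-consistent.

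**The case against.** The strongest reply is that this is a rounding slip with little consequence. The percentage is the main statement and the count is a gloss on it. Statistical Methods asks whether attendance attains "the hypothesized rate"-type figure, and a rate is most naturally read as the 70%. Aim 1 is to examine adherence and is analysed by a univariate summary. No formal test, go/no-go decision or stopping rule depends on it. Once attendance is reported, any reader can see where it lies against both values.

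Most of this stands, and it limits the weight of the point. It does not remove the inconsistency: the wording sets a minimum, the count falls below it, and nothing in the article says that the percentage governs.

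Two stronger readings are tempting and are not supported.

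- **That many participants would be reclassified.** If every participant had the same 70% chance of attending each session, independently, 17.7% would land on exactly 15 sessions, and the share called adherent would be 67% with a bar of 15 against 49% with a bar of 16. But the article defines no per-participant adherence status and gives no attendance distribution. Its Sample Size section cites attrition of up to 33% at 12 months in earlier studies, so attendance is likely to vary widely between people. With a beta-binomial model of mean 70% and an assumed intraclass correlation of 0.1 to 0.4, the share at exactly 15 falls to between 9.3% and 3.7%. The size of any such effect rests on assumptions from outside the article.
- **That the conclusion is open to choice after the data are seen.** This could arise only within the narrow window shown in the working, in a descriptive summary that would itself reveal the position. The article gives no ground for a broader charge.

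**Conclusion.** The inconsistency is real and follows from the article's own figures: 15 of 22 sessions is 68.2%, and a minimum of 70% needs 16 sessions (72.7%). The conclusion rests only on the 22-session denominator, which the article states, and on reading the threshold as a minimum, which is how it is worded.

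Severity is minor. For a group mean, the disputed range is 0.4 of a session, or 1.8 percentage points. For a per-person count, if one is intended, it is the participants at exactly 15 sessions, whose number cannot be derived from the article. The primary outcome (weight), the sample size, the power statement and Aim 2 are untouched.

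A reader might also infer that Aim 1 lacks a properly defined analysis population or a rule for sessions missed after dropout. That is a separate matter, commonly left to a full protocol or analysis plan that is not shown here, and it has no bearing on the choice between 15 and 16. Restricting Aim 1 to those randomised to immediate treatment could also be wrong: waitlist participants later receive the programme, and Hypothesis 2.2 pools both groups.

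**What to change.** Use one threshold, worded identically, in the Aim 1 hypothesis and in Statistical Methods. Either:

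- keep the percentage: at least 70% (at least 16 of 22 sessions); or
- keep the count, if 15 sessions is the intended bar: at least 68% (15/22).

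The choice should be recorded before attendance data are summarised. The cost is a one-line edit in two places. Keeping the percentage makes the bar one session stricter than the printed count; keeping the count lowers the nominal percentage by about two points. Nothing else in the design or analysis needs to change.

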## Methods

### Study Design

The design is a single-phase, assessor-blinded, and waitlist-controlled RCT. Human subjects approval has been received by the Baylor Scott and White Research Institute Institutional Review Board (018-714); the study has been registered on ClinicalTrials.gov (NCT03873467). The intervention design and timeline are outlined in Figure 1.

**Figure figure1:**
[figure not shown]
Enrollment and assessment schedule. GLB: Group Lifestyle Balance.

### Study Setting

Study procedures will be completed at Baylor Scott and White Institute for Rehabilitation, a large rehabilitation hospital in an urban setting in the southwestern United States.

### Participants and Recruitment

The primary sources of recruitment will be Baylor Scott and White Institute for Rehabilitation and community agencies in the Dallas–Fort Worth metroplex. Recruitment will be completed by trained interventionists who are members of the research team, and approaches include in-person visits to community organizations and stroke support groups, flyers, calls, and physician referrals, with a snowball technique for further recruitment. Recruitment will occur over a 4- to 6-month period to ensure that the target sample size is reached.

### Eligibility

Interested participants will contact or be contacted by the research team using information provided on approved study flyers. An eligibility screener will be completed telephonically with the following inclusion criteria: (1) BMI ≥25 kg/m^2^, (2) aged 18 to 85 years, (3) all types of stroke, (4) at least 12 months after stroke, and (5) physician approval to be physically active and make dietary changes. Exclusion criteria are as follows: (1) low cognitive function (<10 on the Cognistat) [19], (2) residing in a hospital, acute rehab setting, or skilled nursing facility, (3) preexisting diagnosis of an eating disorder, (4) pregnancy, (5) taking medication for diabetes, or (6) not fluent in English language. Before the completion of study procedures, informed consent will be obtained by trained research personnel in a private room at Baylor Scott and White Institute for Rehabilitation.

### Intervention

The GLB intervention promotes self-management of a healthy lifestyle based on the tenets of Social Cognitive Theory [20] and the Health Belief Model [21]. The GLB program facilitates individual engagement in health behavior change and is completed in a group setting [11-15]. Data from previous GLB trials have shown 5% to 7% weight loss in a variety of settings, including community centers, churches, worksites, and health care systems [13,16,22-28]. The goal for participants is to reach 150 min of physical activity following the American Heart Association’s (AHA) recommendations and follow dietary guidelines by the United States Department of Agriculture. The GLB program comprises 22 sessions over 12 months, including 12 weekly core program sessions, 4 transition phase sessions, and 6 support sessions (see Multimedia Appendix 1). GLB program materials are made available to the public under the Creative Commons licensing agreement through the Diabetes and Prevention Support Center at the University of Pittsburgh that developed the GLB program.

The GLB curriculum was adapted based on the recommendations from an advisory board of 29 key stakeholders, including stroke survivors, caregivers, clinicians (eg, physicians, therapists, registered dieticians, and neuropsychologists), community partners (eg, AHA and support groups), and researchers, with specific consideration for individuals with stroke (GLB-CVA). The advisory board met to review and discuss relevant changes to the existing curriculum during a 1-day meeting and were compensated US $100 for their time. The recommended modifications were then made by the study team and approved by the Diabetes and Prevention Support Center at the University of Pittsburgh. Modifications included (1) reorganizing and refocusing the content to reflect the importance of healthy behaviors on heart health and prevent recurrent stroke, (2) reducing the volume of content to focus on 2 to 3 main points at each session, (3) involving care partner in the sessions to provide physical and emotional support, (4) developing stroke-specific handouts on weight loss barriers and healthy lifestyle importance, (5) creating and locating handouts and weblinks to modify physical activity and adaptive cooking, and (6) including guest lectures by experts in the field (eg, physical therapist and dietitian). The GLB-CVA intervention will be delivered by trained GLB lifestyle coaches at Baylor Scott and White Institute for Rehabilitation. Training was completed at either the University of Pittsburgh’s Lifestyle Coach Training Workshop or Master Training Center at Baylor Scott and White Health and Wellness Institute. Both sites have recognition by the Centers for Disease Control and Prevention (CDC) as official GLB training centers.

### Outcome Measures

Participants will complete assessments at 4 time points over the course of the yearlong intervention, including baseline, 3, 6, and 12 months. The waitlist control group will complete 2 additional assessment periods that serve as data for comparison in the RCT before they undergo the 12-month intervention. Demographic data collected will include the following: type of stroke, severity of disability (Modified Rankin Scale [29]), current age, date of stroke, sex, parental history of diabetes, race and ethnicity, education level, premorbid history of mental illness, marital and relationship status, diagnosed medical conditions, previous and present smoking and cigarettes per day, alcohol consumption and drinks per week, residence status and zip code, annual household income category, pre- and current stroke insurance type, pre- and current employment status, prestroke and current weight, height, and resting metabolic rate with MedGem. The primary and secondary outcomes are outlined in Multimedia Appendix 2 [30-49]. Participants will be compensated US $25 for their participation at each study time point. Assessments will be completed by a data collector who is trained as a medical assistant and phlebotomist and has completed Modified Rankin Scale training for previous stroke studies.

### Sample Size

For the proposed study, 64 participants (32 per group) will be enrolled. The sample size was calculated to ensure that we have sufficient power for our analyses on the primary outcome (weight). Previous GLB studies with the general population have demonstrated weight loss over time (median *d*=0.99 at 3 months, 0.91 at 6 months, and 0.74 at 12 months) [15-18]. Results also indicated a maximum attrition rate of 16%, 23%, and 33% at 3, 6, and 12 months, respectively. Thus, a sample size of 64 will allow a power of greater than 90% to detect a conservatively assumed group difference of 4% in weight change (95% power). In the event of 33% attrition, we will achieve 83% to 87% power to detect these differences.

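### The stated power for a 4% between-group difference rests on effect sizes for weight loss over time and on an unstated SD of about 4.0 to 4.4 points, which sits badly with calling the 4% conservative

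*Protocol article*

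**What the plan says.** The Sample Size section of the protocol article fixes the size: "64 participants (32 per group) will be enrolled". Its evidence is that earlier GLB studies "demonstrated weight loss over time (median *d*=0.99 at 3 months, 0.91 at 6 months, and 0.74 at 12 months"), with maximum attrition of 16%, 23% and 33% at those times. From this it concludes that "a sample size of 64 will allow a power of greater than 90% to detect a conservatively assumed group difference of 4% in weight change", giving 95% in parentheses, and adds: "In the event of 33% attrition, we will achieve 83% to 87% power to detect these differences".

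The section gives no SD for percent weight change, no alpha and no sidedness, and it does not say how the 4% relates to any of the d values.

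Elsewhere, the Intervention section reports that "Data from previous GLB trials have shown 5% to 7% weight loss in a variety of settings", and the Discussion repeats the 5% to 7%. Hypothesis 2.1 (Objectives, Aim 2) compares the groups at 3 and 6 months. Under Allocation, waitlisted participants start the programme after 6 months.

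**The concern.** A d for loss over time is most naturally read as change within treated participants. The power claim concerns a difference in change between randomised arms, whose standardised size depends on the difference and on the SD of change in both arms. The section moves from the first to the second without a bridging figure.

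The 4% is presented as cautious, and it is indeed below the 5% to 7% reported for earlier programmes. But if the raw effect is discounted and the SD is not, the standardised effect should fall too. The stated power appears to use the full earlier standardised effect.

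At stake is how the result is read. If the true SD is larger than the unstated one, a null result would look more conclusive than the design allows.

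**Working it through.** **Inputs.** 32 per arm; d = 0.99, 0.91 and 0.74; attrition 16%, 23% and 33%; difference 4% (all Sample Size). Earlier loss 5% to 7% (Intervention, Discussion). Assumption: two-sided alpha of 0.05.

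**Method.** Two-sample t-test, n per arm, noncentral t with 2n − 2 degrees of freedom and noncentrality d × √(n/2).

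**Completers per arm.** 32 × 0.84 = 26.9; 32 × 0.77 = 24.6; 32 × 0.67 = 21.4.

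**1. Reproducing the stated figures, with the quoted d as the between-arm effect**

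| d | 32 per arm | 21 per arm | 22 per arm |
|---|---|---|---|
| 0.91 | 94.8% | 82.1% | 83.9% |
| 0.99 | 97.4% | 87.9% | 89.4% |
| 0.74 | 83.0% | 64.8% | 66.9% |

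The 95% and the 83% to 87% are matched by d = 0.91 to 0.99, within about 2 points after attrition.

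**2. The SD this implies for a 4% difference.** SD = difference / d: 4/0.91 = 4.40 and 4/0.99 = 4.04. Working backwards, 95% at 32 per arm needs d = 0.916, so SD = 4/0.916 = 4.37.

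**3. What a discounted effect would give.** Suppose the earlier loss and the d values belong together, d = mean change / SD of change, and both arms share that SD.

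| Loss, d | SD | d for 4% | Power, 32 per arm |
|---|---|---|---|
| 5%, 0.99 | 5/0.99 = 5.05 | 0.79 | 88% |
| 5%, 0.91 | 5/0.91 = 5.49 | 0.73 | 82% |
| 7%, 0.99 | 7/0.99 = 7.07 | 0.57 | 61% |
| 7%, 0.91 | 7/0.91 = 7.69 | 0.52 | 54% |

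**4. Relaxing equal SDs.** Pooled SD = √((SD_treated² + SD_control²)/2).
- 5% loss, d = 0.91, control SD 3 (an assumption): √((5.49² + 3²)/2) = 4.43, power 94.5%.
- 7% loss, d = 0.99, control SD 0: √(7.07²/2) = 5.0, power about 88%.

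So a less variable control arm can restore about 95% at the 5% end. At the 7% end power stays below 90% even with no variation among controls.

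**5. Power for 4% at the attrition that applies to the randomised comparison**

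| Pooled SD | 27 per arm (16%, 3 months) | 24 to 25 per arm (23%, 6 months) |
|---|---|---|
| 4.4 | 91% | 87% to 88% |
| 5.5 | 75% | 69% to 71% |
| 7.7 | 47% | 42% to 44% |

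**The case against.** The strongest reply is that a match is not a derivation. Any pooled SD of about 4.1 to 4.4 points yields the stated powers without a pre-post d, and one-sided 5% with d of about 0.83 comes close (95% at 32 per arm, 84% to 86% after attrition). This stands: a reader might infer that the figures can arise only from a misused over-time d, and the article does not show that.

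Second, the 5% to 7% and the d values cite largely different references (only one is common), and the 5% to 7% has no time point. Step 3 is therefore a conditional calculation. A reader might infer from it that no pairing of the article's figures reaches 90%; step 4 shows that this fails once control-arm change may be less variable.

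Third, the planned analysis is a covariate-adjusted growth model, not a t-test. As an illustration, averaging the 3- and 6-month visits with an assumed correlation of 0.7 lifts the 88% case to about 92%. That gain is possible, but the Sample Size section claims none.

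Fourth, a reader might pair 33% attrition with the 12-month d of 0.74 and conclude that the true power is 65% to 67%. The text ties 83% to 87% to the 4% difference, not to that d, and for a fixed effect the highest attrition is a cautious choice. What remains is that 33% does not belong to the 3- and 6-month comparison.

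Finally, a condensed article may leave the SD and alpha to the full protocol. Their absence alone would be no finding. The point is that the published powers do not follow from the basis printed beside them.

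**Conclusion.** The point holds in limited form: the stated power is not supported by its quoted basis. The figures coincide with over-time d values of 0.91 to 0.99 used as a between-arm effect, and they need a pooled SD that the article neither states nor justifies. On the three assumptions in step 3, the 4% is not conservative in standardised terms, and power without attrition falls short of the stated 95% by about 7 to 41 points (95 − 88; 95 − 54).

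The documents do not establish that the true power is low or that 64 participants are too few. With a pooled SD near 4.4 the 95% is correct at full enrolment. The article gives no means of telling which case applies, so one favourable figure should not stand alone.

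**What to change.** Keep N = 64 and rewrite the power paragraph:

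- State the SD of percent weight change, alpha with sidedness, and the time point behind the 4% difference. Say where the SD comes from and whether it is assumed equal in both arms.
- Do not use the over-time d as the between-arm effect. If the d values stay as background, say what they measure and reconcile them with the 4%.
- Replace the single 95% and 83% to 87% claims with a range at the 3- and 6-month attrition. For example: with 24 to 25 completers per arm (23% attrition), two-sided 5%, power for a 4% difference is about 87% to 88% if the SD is 4.4 points, 69% to 71% if 5.5, and 42% to 44% if 7.7.
- If a gain from the repeated-measures model is claimed, state the correlation assumed.

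This is a change of wording with no added participants. Its cost is a less favourable stated power.
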